## Abstract

The coronavirus disease 2019 (COVID-19) pandemic increased education-related distress among University students globally, including in Indonesia. Psychological factors, such as academic demands, limited opportunity to meet their peers, problematic use of technology, and domestic problems, influenced the well-being of the students, leading to poor academic performance. A mobile-based counseling application was developed to address the distress among University students. The application was meant to reach students living remotely to enable them to access psychological assistance. Therefore, the purpose of this study was to describe a protocol aimed to evaluate the equivalence of the application when compared to the Treatment-As-Usual (TAU) in increasing the coping self-efficacy (CSE) and resilience of students as well as in decreasing their level of depression. A two-armed parallel randomized control non-inferiority trial will be conducted among approximately 430 students with selected academic problems. The participants will be randomly allocated into the TAU and the intervention groups. The primary and secondary outcomes will be measured by the Indonesian versions of the Coping Self-Efficacy (CSE) Scale, the Resilience Scale (RS-14), and the Patient Health Questionnaire (PHQ-9). The data will be collected at baseline, at the end of each session, and after 3 months. The outcomes will be analyzed using repeated-measures ANOVAs, intention-to-treat, and per-protocol analysis. If proven, the application will be used as an alternative media in helping the students.

**Clinical Trial Registration:** Thailand Clinical Trials Registry (TCTR20200530001); Date of registration: May 28, 2020.

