### Participants

The target population in the study will be University students who have academic-related psychological problems. The inclusion criteria of the sample are a University student, aged 18–25 years old, having academic-related problem(s), and registering as a participant in this study. The academic-related problems that will be included in the study are (1) (educational) adjustment difficulties; (2) difficulties in writing a thesis; (3) academic procrastination; (4) poor self-regulation for learning; and (5) a low grade point average (GPA). The study will exclude students with (1) physical disabilities; (2) under the care of mental health professionals; and (3) the score of PHQ-9 more than 14 (having severe depression), (Rahmadiana et al., 2019).

The participants of the study will be those who register in a University counseling center. They will be then screened with the PHQ-9. If they are willing to participate in the study, the research assistants will give informed consent and the right to withdraw from the study at any given time they wish to. The students who decline to join the study or withdraw from the study will be followed up to identify their reasons for declining and withdrawing from the study. The students have a right to undergo post-trial treatment if needed.

The sample size is a sensitive issue in the non-inferiority trial (Hahn, 2012). Large sample size is usually needed. However, if the new intervention is assumed to be slightly more effective than the TAU, the number of samples can be reduced. The mobile-based counseling application can be assumed to be more practical for the students in this country. Those who live remotely can still access the psychological services. The data from the University counseling center in 2020 were also a source of consideration in determining the sample size. The center admitted 482 clients in that year, with an average of 40 clients per month. With 80% CI, the expected SD will be one, and the inferiority margin (Δ) will be 0.24. It was calculated that the number of participants per arm needs to be 215 and the total sample size needs to be 430.

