### Determining an Inferiority Margin of the Trial

In the non-inferiority trial, the researchers need to determine Δ (Hahn, 2012). In this study, the margin is the maximum acceptable extent of non-inferiority of the mobile-based counseling application. The maximum limit of Δ can be set to the entire effect size of the active control treatment (Hahn, 2012). Several proposals for choosing the inferiority margins in the context of SFBT have been made (Table 1). There are several suggestions for the maximum difference in outcomes that will be considered clinically irrelevant. It ranges from *d* = 0.17 to *d* = 1.76. The smallest margin was suggested by Schmit et al. (2016), (*d* = 0.24) for the treatment of internalizing disorders. Thus, in this study, it was decided to use the inferior margin of 0.22 (i.e., the inferior margin up to 0.22), corresponding to a small effect size.

**Table 1 T1:** The effect size from the solution-focused brief therapy (SFBT)-related studies.

**Previous studies**	**Effect size**
Impacts on academic and emotional difficulties (Daki and Savage, 2010)	≈0.13 (partial eta squared, medium effect size)
Meta-analysis of solution-focused brief therapy for treating symptoms of internalizing disorders (Schmit et al., 2016)	≈0.24 (Hedges' g, small effect size)
Examining the effectiveness of solution-focused brief therapy: a meta-analysis (Kim, 2008)	0.26–0.38 (Cohen's *d*, small effect size)
SFBT for health-related psychosocial outcomes (Zhang et al., 2018)	0.34 (Cohen's *d*, small effect size)
Solution-focused brief therapy in schools: A review of the outcome literature (Kim and Franklin, 2009)	0.38–1.76 (Cohen's *d*, medium to large effect size)

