### Data Analysis

Descriptive statistics will be used to describe relevant demographic data, such as the frequency and the percentage for the categorical data as well as the mean and the SD for the outcome measurements. There will be three analysis plans to prove the non-inferiority of the application, which are (1) repeated-measures ANOVAs (Goodman et al., 2016; Twisk et al., 2018), which will be used to test for differences between the TAU and the intervention groups (i.e., between-subjects factor) in the treatment at the four time points (i.e., within-subjects factor). We would like to assess whether the outcomes will be improved after treatment using the application and the TAU. An analysis will be conducted to check the constancy assumption. Then, both (2) the intention-to-treat (ITT) and (3) the per-protocol analysis will be performed. Previous studies showed that performing both analyses will produce more convincing results to conclude the non-inferiority of a new treatment (Hahn, 2012; Walker, 2019). The ITT analyses will be chosen to handle the missing value due to the protocol deviations, withdrawal, and non-compliance (Gupta, 2011) whereas the per-protocol analysis will minimize the factors that would make the two groups seem similar (Walker, 2019).

The statistical hypotheses in this non-inferiority trial use Δ. The null hypothesis states that the intervention using the application will be inferior to the TAU (H0: TAU–SAENA ≥ Δ). The alternative hypothesis states that the intervention will not be inferior (will have a similar effect) to the TAU although the effect may not be as good as the TAU within the extent of margin (H1: TAU–SAENA < Δ). Of note, 95% CI will be used. The interval will be the mean difference between the outcome measures of the two groups. The formula is as follows:

$$\begin{array}{l} \left(\mu_{saena}-\;\mu_{TAU}\right)\pm 1.96\sqrt{\frac{\sigma_{saena}^{2}}{n_{saena}}+\frac{\sigma_{TAU}^{2}}{n_{TAU}}} \end{array}$$

μ, mean; Tau, standard deviation; *n*, sample.

The 1.96 is the *z*-value, and the value from this formula can now be compared with Δ. If the interval remains above Δ, then the inferiority of the application will be proven according to the standards that have been set. In contrast, if the upper limit for treatment difference by the intervention group compared to the TAU group is < Δ, then the non-inferiority will be concluded.

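### The 215 per arm contains no allowance for loss, so the implied 80% power is not delivered in the per-protocol set, and the power should be restated under the decision rule the plan actually uses

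*Protocol article*

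**What the plan says.** All references are to the protocol article.

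- **Participants** gives the sizing inputs, "With 80% CI, the expected SD will be one, and the inferiority margin (Δ) will be 0.24", and the result, "It was calculated that the number of participants per arm needs to be 215 and the total sample size needs to be 430". No loss rate or inflation is mentioned. The same section lets students withdraw whenever they wish.
- **Abstract** uses the same figure as the size of the trial, which "will be conducted among approximately 430 students with selected academic problems".
- **Data Analysis** foresees loss: "The ITT analyses will be chosen to handle the missing value due to the protocol deviations, withdrawal, and non-compliance". It plans both an ITT and a per-protocol analysis, on the ground that "performing both analyses will produce more convincing results to conclude the non-inferiority of a new treatment".
- **Data Analysis** also fixes the interval, "Of note, 95% CI will be used", with 1.96 in the formula.
- **Determining an Inferiority Margin of the Trial** gives a different margin from the sizing: "it was decided to use the inferior margin of 0.22 (i.e., the inferior margin up to 0.22), corresponding to a small effect size".
- **Discussion** accepts that the number of participants may be limited but says that the study is not short of power.

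**The concern.** A sample-size formula for a difference in means returns the number of people who contribute data to the comparison. Here the same number serves as the requirement and as the enrolment, so the calculation holds only if every student contributes an analysable outcome. The plan does not expect that, and one of its analyses excludes students by design.

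In a non-inferiority trial, a smaller analysed set widens the interval and makes it more likely that an app truly equal to treatment as usual fails to show it. The per-protocol analysis is the plan's guard against the two groups looking falsely similar. It is also the set most certain to fall below 215 per arm, and its power is not stated. Readers of the Discussion are told that power is sufficient.

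**Working it through.** **Inputs.** SD 1, margin 0.24 and 80% come from Participants. The article calls the 80% a CI; it is read here as power because that reading reproduces the stated number. Allocation is 1:1, implied by 215 and 430. The article gives no significance level for the sizing and no number for the true difference; one-sided 5% and a difference of 0 are the values that reproduce 215.

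**Step 1: reproduce 215.**

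n per arm = 2 × ((z₁₋α + z_power) × SD / Δ)² = 2 × ((1.645 + 0.842) / 0.24)² = 214.67, rounded up to 215.

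The match is exact with zero loss. Other combinations do not give 215:

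- margin 0.24, one-sided 2.5%: 273
- margin 0.22, one-sided 5%: 256
- margin 0.22, one-sided 2.5%: 325

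**Step 2: look for a reserve.** An allowance for a fraction x lost divides by (1 − x). On the same inputs, enrolment would be 227 per arm at 5% loss, 239 at 10% and 269 at 20%. The printed figure is the uninflated one.

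**Step 3: power when a fraction x of the 215 per arm is not analysed.** The article gives no rate, so x is an assumed range.

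Power = Φ( Δ × √(215(1 − x) / 2) − z ), with SD 1 and true difference 0.

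Three settings are shown:

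- A: the sizing assumptions (Δ = 0.24, z = 1.645)
- B: the interval in Data Analysis (Δ = 0.24, z = 1.96)
- C: that interval with the margin section's value (Δ = 0.22, z = 1.96)

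| Loss x | Analysed per arm | A | B | C |
|---|---|---|---|---|
| 0% | 215 | 80% | 70% | 63% |
| 5% | 204 | 78% | 68% | 60% |
| 10% | 193.5 | 76% | 66% | 58% |
| 15% | 183 | 74% | 63% | 56% |
| 20% | 172 | 72% | 60% | 53% |
| 30% | 150.5 | 67% | 55% | 48% |

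Example, 20% loss: √(172 / 2) = 9.274. Setting A: 0.24 × 9.274 − 1.645 = 0.581, power 71.9%. Setting B: 0.24 × 9.274 − 1.96 = 0.266, power 60.5%. Setting C: 0.22 × 9.274 − 1.96 = 0.080, power 53.2%.

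**Step 4: separate the causes.** Moving from A to B with complete data costs about 10 points (80.1% to 70.1%). Moving to C brings the figure to 62.6%. A 10% loss costs about 4 points in setting A (80.1% to 76.3%) and about 5 in B (70.1% to 65.6%). Loss is therefore one contributor, and at modest rates it is smaller than the mismatch between the sizing and the planned interval.

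**The case against.** Several stronger readings are tempting, and the article does not support them.

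- **That loss alone takes the trial below 80%.** It does not. Under the planned 95% CI, power is 70.1% before anyone leaves. Quoting 72% at 20% loss would overstate the planned test, whose power there is 60.5%, or 53.2% at margin 0.22. This objection stands, and it determines how the power must be restated.
- **That 80% power is a stated target.** The article writes 80% CI. Power is an inference, though it is the reading that gives 215.
- **That a material loss rate is established.** A right to withdraw and a reason for choosing ITT are not forecasts. At 5% loss the cost on the sizing assumptions is under 2 points. The size of the effect is conditional on the rate assumed.
- **That the ITT set shrinks to 215(1 − x).** ITT is said to be the means of handling missing values, and the method may be set out in a document not shown. The ITT shortfall is therefore open. The per-protocol one is not, once any student is excluded.
- **That every student must reach the visit 3 months after the last session.** The article does not fix that visit as the time of the primary comparison. If the comparison is at the end of the sessions, later loss does not reduce its number.
- **That non-inferiority must be shown in both sets.** The article says that doing both is more convincing; it does not make success in both the rule. Joint-power figures would answer a rule that is not stated.

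It can also be said that an article condenses its protocol, so a dropout allowance may merely have gone unmentioned. The exact match in step 1 answers this: the printed total is the uninflated number. Participants also suggests that the app might be assumed slightly better, which could act as a reserve. It gives no number, and a difference of 0 already yields 215.

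**Conclusion.** The point holds in a limited form. The arithmetic behind 215 is right. The fault is that an analysable number serves as the enrolment in a plan that foresees loss and tests a per-protocol set. The implied 80% is not delivered at least in that set, and the Discussion's assurance on power is not supported.

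Over an assumed 5% to 30% loss, power is 78% to 67% on the sizing assumptions, 68% to 55% under the 95% CI that the plan uses, and 60% to 48% if the margin is also 0.22. These figures rest on SD 1, a true difference of 0, a normal approximation and equal loss in both arms. The second and third ranges describe the planned test; the first only isolates the effect of loss on the sizing as done. Correcting for loss alone would not restore 80%.

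**What to change.** Keep 430 enrolled and make these changes to the text:

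1. In Participants, present 430 as the number enrolled. State an assumed proportion without an analysable primary outcome and the resulting number per arm, 215(1 − x). Do the same for the per-protocol set.
2. Give the power for the ITT set and for the per-protocol set under the decision rule in Data Analysis (95% CI, z = 1.96) and one margin, after reconciling 0.24 with 0.22. Do not use one-sided 5% for this. For example, at margin 0.24 with 20% not analysed: 172 per arm, power about 60%.
3. Amend the statement on power in the Discussion to match.
4. Report joint ITT and per-protocol power only if success in both sets is made the rule.

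This takes a few sentences and no added recruitment. The downside is a less favourable stated power. Regaining 80% by enrolment would be a much larger change: under the 95% CI, 273 per arm at margin 0.24 or 325 at 0.22 before any loss, against 482 clients admitted by the centre in 2020.

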### Randomization

The participants who will be randomized are the students who register as clients at the University counseling center, meet the inclusion criteria, and are willing to participate in this study. The randomization will be carried out by the research assistants using a computerized random number generator. The results from the randomization are a list of registration numbers that will be categorized as the intervention group and the control group. The participants will be then assigned to those two groups based on their registration numbers. The allocation will be performed before the initial assessment.

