## Materials and Methods

### Study Design

This study describes a study that will be conducted as a two-armed parallel randomized controlled non-inferiority trial. The trial is in line with the guidelines for the protocol content of the non-inferiority trial (Piaggio et al., 2012). It will also be based on the guidance of the Standard Protocol Items: Recommendations for Intervention Trials (SPIRIT) Statement (Tetzlaff et al., 2012; Chan et al., 2013). The non-inferiority scheme will be used in this study because the application is not aimed to be more powerful or effective than the usual treatment but aimed to increase the practicality of the counselors to store the data in the application and to hide personal contacts (e.g., email addresses or online meeting IDs) by solely using the application only for the counseling purposes (Hahn, 2012).

To eliminate the assay sensitivity, bias, and constancy assumption (ABC) of this non-inferiority trial, there are several things included in the design. First, the outcome measurement tools that will be used in both groups are reliable. Second, besides using randomizing in allocation and double-blinding procedure, the control group will get the TAU without any intervention to prevent a bias. Third, the data will be collected in the same period for both groups to minimize any situational effects, such as the COVID-19 pandemic-related government policies in this country (Walker, 2019).

The proposed study will be a parallel group design comparing two types of treatments. The intervention group will use the application whereas the control group will get the TAU. The intervention group will have three counseling sessions for a month; meanwhile, the control group will have many sessions based on the need of each individual. All outcomes will be assessed repeatedly using online self-reported forms, which will be facilitated by research assistants. The assessments will be taken (1) before the intervention, (2) after each session (a session/week), and (3) after 3 months. The study design is shown in Figure 1.

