### Outcome Measurements

The participants in the intervention group will complete the assessments at (1) the baseline (T0); (2) at the end of the first counseling session (T1); (3) at the end of the second counseling session (T2); (4) at the end of the third counseling session (T3); and (5) 3 months after the third counseling session (T4). There will be a week interval between the counseling sessions (T1, T2, and T3). Meanwhile, the participants in the control group will be measured at 3–5 points in time depends on the number of counseling sessions they have. They will fill the questionnaires at (1) the baseline (T0); (2) at the end of their counseling session(s), (T1 and/or T2 and/or T3, etc.); and (3) 3 months after the last session (TX). The data will be collected using the online forms and will be assisted by the research assistants.

The primary outcome of the proposed study will be CSE measured by the Coping Self-Efficacy (CSE) Scale. The Indonesian version of the CSE consists of 26 items with 11-point scale (0–10). The scale has good reliability (*r* = 0.92), (Nurhidayah, 2020). The total score will be used as an indicator of the level of CSE of participants. The CSE is defined as a belief about own ability of an individual to perform specific coping behavior (Chesney et al., 2006). Self-efficacy serves as evidence in measuring changes in the coping ability of individuals, especially for those who seek professionals to solve their problems (Chesney et al., 2006; Yoo et al., 2020).

The secondary outcomes of this study will be (1) resilience and (2) level of depression. Resilience is defined as the capacity of a dynamic system to adapt successfully to adversity that threatens system function (Masten, 2014). The Resilience Scale (RS-14), (Surzykiewicz et al., 2019), which will be used to measure this variable, has five dimensions, namely, equanimity, perseverance, self-reliance, meaningfulness, and existential aloneness. The short version of the RS test has been adapted to the Indonesian language. It has 14 items with a 7-point Likert scale (*r* = 0.87). The scale has good Construct Validity Fitness Indexes [Non Normed Fit Index (NNFI) = 0.99, Root Mean Square Error of Approximation (RMSEA) = 0.027, and Standardized Root Mean Residual (SRMR) = 0.026], (Valentino, 2021).

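### Allocation precedes the T0 questionnaires, so the coping self-efficacy and resilience baselines are pre-treatment but not pre-randomisation

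*Protocol article*

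**What the plan says.** All references are to the protocol article.

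- **Order of steps.** Randomization: "The allocation will be performed before the initial assessment". Those randomised are registered clients who "meet the inclusion criteria, and are willing to participate in this study".
- **Screening.** Participants, on students registering at the counselling centre: "They will be then screened with the PHQ-9". A score above 14 excludes, so this PHQ-9 score exists before allocation.
- **Baseline.** Outcome Measurements makes T0 the first assessment in both arms. For the application arm: "The participants in the intervention group will complete the assessments at (1) the baseline (T0"). For the control arm: "They will fill the questionnaires at (1) the baseline (T0"). Study Design places this assessment before the intervention.
- **Mode of assessment.** Study Design: "All outcomes will be assessed repeatedly using online self-reported forms, which will be facilitated by research assistants".
- **Who allocates.** Randomization: "The randomization will be carried out by the research assistants using a computerized random number generator".
- **Blinding.** Study Design, among the steps against bias: "besides using randomizing in allocation and double-blinding procedure, the control group will get the TAU". The article does not say who is blinded, how, or until when.
- **Analysis.** Data Analysis plans a repeated-measures ANOVA over four time points, and a 95% confidence interval for the difference between two group means, compared with the margin.

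**The concern.** A baseline collected before allocation cannot be affected by the allocation. One collected afterwards loses that guarantee, and three features of this trial make the loss relevant.

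First, CSE is a self-rated belief in one's own coping ability, which hope or disappointment about the assigned arm could move. Second, an application with three sessions and usual counselling with sessions by need are easy to tell apart, so blinding students is hard to sustain once the arm is known. Third, the role that runs the randomisation also helps students with the forms.

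Two consequences follow. If the arms' T0 scores are displaced differently, any contrast that uses T0 inherits the displacement, and the margin is small (0.22 or 0.24 SD). And a student who leaves after allocation but before T0 has no CSE or RS-14 baseline, with nothing to ensure that such loss is equal between arms.

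**Working it through.** **1. Which assessment follows allocation?** Randomization admits only students who already meet the criteria, and the PHQ-9 cutoff is one of them. Screening therefore precedes allocation, and the initial assessment that follows it is most naturally T0. The sequence is: register, PHQ-9 screen, consent, allocation, T0, first session. Nothing in the text says that the arm is withheld until T0 is complete.

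**2. Which outcomes have a pre-allocation value?** PHQ-9 does, from screening. None is described for CSE or RS-14.

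**3. Which analyses use T0?**
- *Repeated-measures ANOVA:* Outcome Measurements lists five assessments in the application arm (T0 to T4) and three to five in the control arm. Data Analysis uses four without naming them. The stated wish to see whether outcomes improve after treatment suggests that T0 is included, but the text does not say so.
- *Confidence interval:* the formula has two means, two variances and two sample sizes, with no baseline term. Applied to post-treatment means alone, it does not use T0.
- *Change-from-baseline or baseline-adjusted contrasts:* these would use T0, but the article specifies none.

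**4. The plan's own figure.** With margin 0.24, SD 1, no true difference, one-sided 5% and the stated 80% read as power (an assumption):

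n per arm = 2 × (1.645 + 0.842)² / 0.24² ≈ 214.7, rounded up to 215.

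This matches the stated 215 per arm and 430 in total. The point here does not depend on it; it supplies the scale (SD units) and the n used below.

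**5. Scale of a possible bias (illustration only).** Let s be the displacement of T0 in the application arm minus that in the TAU arm, in SD units. The document gives no value; 0.05 to 0.20 in absolute size is assumed.

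- Change contrast: bias = −s.
- Baseline-adjusted contrast: bias = −ρs, where ρ is the baseline-to-follow-up correlation (assumed 0.5 to 0.7, equal SDs).

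| Absolute s | Share of 0.22 | Share of 0.24 |
|---|---|---|
| 0.05 | 0.05/0.22 = 23% | 0.05/0.24 = 21% |
| 0.10 | 0.10/0.22 = 45% | 0.10/0.24 = 42% |
| 0.20 | 0.20/0.22 = 91% | 0.20/0.24 = 83% |

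The shares are for the change contrast; multiply by ρ for the adjusted one.

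**6. What that would do to the decision, if it used T0.** Take 215 per arm and z = 1.96. The standard error of the change contrast is √[2(1 − ρ) × 2/215], which is 0.096 at ρ = 0.5 and 0.075 at ρ = 0.7. That of the adjusted contrast is √[(1 − ρ²) × 2/215], which is 0.084 and 0.069.

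- *Shift favouring the application (s negative).* The false non-inferiority rate is Φ(|bias|/SE − 1.96), against a nominal 2.5%.
- *Shift against the application (s positive).* For the change contrast with margin 0.24 and no true difference, power is Φ((0.24 − |s|)/SE − 1.96). Without a shift it is 70% at ρ = 0.5 and 90% at ρ = 0.7.

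| Absolute s | False non-inferiority, change | False non-inferiority, adjusted | Power, change, opposite shift |
|---|---|---|---|
| 0.05 | 8% to 10% | 5% to 7% | 50% to 72% |
| 0.10 | 18% to 27% | 9% to 17% | 31% to 47% |
| 0.20 | 55% to 76% | 22% to 53% | 6% to 8% |

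Ranges run from ρ = 0.5 to ρ = 0.7.

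**The case against.** **Allocation is not disclosure.** Randomization describes a list of registration numbers split into two groups, and double-blinding is named. A reader might infer that students are told their arm before T0; the text does not say that. T0 comes before any session, so withholding the arm until then is feasible. This stands, and it limits the point to a risk that the plan leaves open. It does not remove it: no concealment step is described, and the assistants who randomise share a role with those who help with the forms.

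**The non-inferiority decision may not use T0.** A reader might infer that the main conclusion is compromised. The interval formula has no baseline term, so on post-treatment means alone it is untouched. This stands.

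**The size and direction are assumed.** Both stand. If students prefer the application, its T0 could rise or that of TAU could fall, which works against concluding non-inferiority. The opposite reaction would favour it. The tables show scale, not expected bias.

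**PHQ-9 has a clean earlier value.** Correct. The point is confined to CSE and RS-14.

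**Intention-to-treat analysis is planned and withdrawals are followed up.** A reader might infer that early leavers are dropped, so that the analysed groups are no longer those randomised. The article does not say so, and handling of missing baselines may properly sit in an analysis plan. What stands is narrower: under this order such students would have no CSE or RS-14 baseline.

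**Conclusion.** The point holds as one of sequence. T0 for CSE and RS-14 is collected after allocation, so those baselines are pre-treatment but not pre-randomisation, and the plan describes nothing that protects them from knowledge of the arm. The repeated-measures ANOVA is exposed if T0 is among its four time points, as is any change-from-baseline or baseline-adjusted contrast.

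It is not shown that the baselines will be biased, or in which direction. If the arms' T0 scores were displaced by 0.05 to 0.20 SD relative to each other (assumed), a change contrast would be off by 23% to 91% of the 0.22 margin, or 21% to 83% of 0.24. The conclusion also assumes that the initial assessment means T0, which the eligibility sequence supports. It rests on the text alone, since the study design figure could not be consulted. The change is worth making because the protection is almost free.

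**What to change.** 1. Amend Randomization so that PHQ-9 screening, consent and submission of the T0 form all come before allocation is made. T0 is an online form, so its submission can trigger assignment.
2. If the list must be generated earlier, state that the allocation is not released to students, or to the assistants helping with the forms, until T0 has been submitted. This protects the T0 answers, although a student lost before T0 would still lack CSE and RS-14 baselines.
3. Reconcile this with the double-blinding statement in Study Design: say who is blinded, to what, and until when.
4. Keep everyone allocated in the intention-to-treat set.

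Cost: two existing steps change order, with no added visit or questionnaire. The second option also needs the list to be held by an automated release or by someone who does not help with the forms.
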